## **II. Research Plan and Design**

**A. Study Objectives:** The broad research goal of this study is to provide novel data regarding the potential efficacy of multimodal exercise to reduce frailty in pwMS and will set the foundation for our long-term goal of identifying novel interventions to improve the quality of life of persons with MS. The specific aims of the project will be to determine the feasibility of a multimodal exercise training in pwMS (Aim 1), and to explore the effects of the multimodal exercise training on frailty in pwMS (Aim 2).

**B. Study Type and Design:** Using a pilot single-blind randomized controlled trial (RCT) study design, ambulatory individuals living with MS will be allocated to 6 weeks of multimodal exercise training (n=30) or to a waitlist control group (n=30) (Figure 1).

[figure not shown]

Figure 1. Study design.

The following outcomes will be collected to accomplish the study aims:

**Aim 1: Feasibility Outcomes:** The following outcomes, based on the guiding principles for feasibility studies, will be utilized to examine the feasibility of the Virtual Reality and Resistance Training for MS (VRRT4MS) program in the study population: a) participant recruitment, i.e., number of consented individuals/number of approached individuals (expressed as a percentage); b) retention rate, i.e., number of participants completing the intervention/number of participants enrolled at baseline (expressed as percentage); c) appropriateness of data collection and training procedures, as quantified through the percentage of missing data for analysis purposes (i.e., missing items in the frailty index) and through time spent in training, respectively; d) participant safety, i.e., number of adverse and serious adverse outcomes throughout the study and self-reported pain, assessed by the numeric pain rating scale, during each training session (the Borg and Omni scales of perceived exertion will also be administered throughout each training session to differentiate exertion from pain); e) evaluation of resources, i.e., difference between proposed and actual research timeline; f) user engagement, i.e., study participant feedback questionnaire. We note that the effects of VRRT4MS on the primary frailty outcome, namely the frailty index (AIM 2), will also represent a further feasibility outcome of the intervention.

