| Biomarkers                     | 12            | Laboratory tests                                  | NfL, BDNF, GFAP, CRP, IL-6, IL-10, TNF-alpha, IFN-gamma, and CXCL9, mi-RNAs.                                                                                                  |

**Legend:** ADL: activities of daily living, MSQoL-54: 54-item multiple sclerosis quality of life questionnaire, MFIS: modified fatigue impact scale, CVLT-II: California verbal

learning test, SDMT: symbol digit modalities test, BVMT: brief visuospatial memory test; TMT: trail making test, 6MWT: 6-minute walk test, BP: blood pressure, BMI: body mass index, CRP: c-reactive protein.

All study outcomes will be assessed in a standardized manner during Visit 2 and 3. Following visit 2, participants will be randomized to one of the two groups based on pre-generated randomization codes prepared by the biostatistician. In accordance with the CONSORT guidelines, sequence generation, allocation concealment and group allocation will be blinded and separate processes. Participants will then either complete the waitlist period (passive control) or attend the exercise training visits 3 times a week, for 6 weeks, totaling 18 training visits. Each training visit will last one hour. The training visits will take place at the Laboratory for Advanced Rehabilitation Research in Simulation at the University of Kansas Medical Center.

**Intervention (Multimodal exercise) Group:** Participants will complete 15 minutes of virtual reality treadmill training (VRTT), followed by 30 minutes of progressive evidence-based resistance training (RT), followed by other 15 minutes of VRTT. This interval training design was chosen to induce acute fatigue before the last bout of VRTT. See Table 2.

**Table 2.** The Multimodal exercise program.

| Exercise components      | Duration   | Description                                                                                                                    | Target (frailty domains)*             |
|--------------------------|------------|--------------------------------------------------------------------------------------------------------------------------------|---------------------------------------|
| 1) VR treadmill training | 15 minutes | Treadmill walking with interactive virtual environment.                                                                        | - Slowness
- Cognition             |

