| 2) RT                    | 30 minutes | Seated leg press, seated hamstring curls, seated calf raises, seated chest press, seated lat-pulldowns, seated shoulder press. | - Muscle weakness
- Shrinkage      |
| 3) VR treadmill training | 15 minutes | Treadmill walking with interactive virtual environment.                                                                        | - Slowness, Cognition
- Exhaustion |

**Legend:** VR: virtual reality, RT: resistance training, \* The multimodal exercise program will also inherently target the 'inactivity' component of frailty.

Both the VR and RT components of the program will be individualized based on the participant's abilities and the training progression will be adjusted every 2 weeks. Over-ground gait speed will be assessed prior to the intervention and every two weeks thereafter and will be utilized to set the treadmill speed for the VR component. As part of VR, participants will navigate through a virtual environment projected on a TV screen while receiving feedback from the system (Figure 2). The RT component will consist of performing evidence-based RT exercises, as fully described in Table 2. In the event participants are unable to complete 15 minutes of continuous walking, walking duration will be progressively increased in 1–3-minute bouts until the prescribed time is reached. The estimated 1-repetition maximum (1-RM) of all RT exercises will be evaluated using validated standard procedures (for untrained individuals) prior to the intervention. At the beginning of the intervention, participants will complete 3 sets of 8-12 repetitions at 20-30% of the 1RM and slowly progress up to 80% over the course of 8 weeks. The end point of each set will always be limited to volitional fatigue. Recovery periods of 2-4 minutes will be prescribed between sets and exercises.

**Control Group:** Participants randomized to the control group will be put on a waitlist (passive control group) for 6 weeks. Upon completion of Visit 3, participants in the control group will be able to receive the intervention, if they wish so.

[figure not shown]

Panel A

[figure not shown]

Panel B

Figure 2. Gait Better (TM) virtual reality (VR) treadmill training set up. Panel A. Camera detects markers on feet and projects them on screen. Panel B. View of VR monitor depicting individual's virtual feet, visual distractors, and obstacles.

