asked to complete exercises that they feel comfortable with. Additionally, the intervention program will be individualized based on the participant's abilities and will be readjusted every two weeks. Given the high rate of fatigue in persons with MS, it is possible that participants will become fatigued during study visits. To mitigate the risk of fatigue, participants will be given ample opportunity for rest during study visits. It is also likely that participants in the intervention group will experience temporary muscle soreness due to the resistance training aspect of the program. Each exercise session will begin and end with stretching to further minimize the risk of muscle pain. In addition, we will monitor perceived exertion through the Borg and Omni scales during each training session. We will also evaluate pain through the numeric pain rating scale during each training session (to differentiate this symptom from perceived exertion). If a participant reports a score higher than 3 on the numeric pain rating scale, we will stop the training session. To minimize the risk of musculoskeletal discomfort during maximal strength testing (1-RM assessment), we will use validated standard procedures for untrained individuals. To prevent participants from falling, participants will be encouraged to take a break if they feel tired, unwell, or dizzy. Participants will be spotted by a member of the research team and will wear an overhead harness that can be used to stabilize a participant if they were to become unsteady. In terms of the risks presented by the blood draw, the researchers will work to mitigate those risks by having the blood draw performed by trained clinicians in a sterile, cleaned environment, therefore minimizing risks.

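### The resistance prescription contradicts itself: an 8-week load progression in a 6-week programme, and, for all six exercises, at least 34 minutes of rest in a 30-minute block

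*Protocol*

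**What the plan says.** **Programme length.** Section II.B says that participants "will be allocated to 6 weeks of multimodal exercise training (n=30") or to a waitlist. Section II.E.2 has the exercise group "attend the exercise training visits 3 times a week, for 6 weeks, totaling 18 training visits", each lasting one hour, and sets the waitlist at 6 weeks too. Section III.G pays for 18 training visits.

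**Load progression.** Below Table 2, II.E.2 says that at the start "participants will complete 3 sets of 8-12 repetitions at 20-30% of the 1RM", and that they then "slowly progress up to 80% over the course of 8 weeks".

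**Session content.** A visit is 15 minutes of virtual reality treadmill walking, "followed by 30 minutes of progressive evidence-based resistance training (RT"), then 15 more minutes on the treadmill. Table 2 describes the resistance part as "Seated leg press, seated hamstring curls, seated calf raises, seated chest press, seated lat-pulldowns, seated shoulder press". On rest: "Recovery periods of 2-4 minutes will be prescribed between sets and exercises". Section II.F.1 adds, as a safety measure: "Each exercise session will begin and end with stretching".

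**Use of the sessions.** Sections II.C.1 and V.B call the intervention feasible if retention and the proportion of completed sessions both exceed 80%. Section II.B makes time spent in training a feasibility outcome. Aim 1 says that the trial will yield effect sizes for a fully powered trial.

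**The concern.** The prescription conflicts with the rest of the protocol in two places. The load progression has an end point that the programme never reaches. And the exercises, sets and rests, taken together, need more time than the block allotted to them.

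What is at stake is the meaning of the dose. Staff who follow this text must depart from it somewhere: fewer exercises, fewer sets, shorter rests, a longer visit, or a faster or truncated progression. The protocol does not say which, so staff may choose differently from one another and between participants. Time in training would then be compared with a target that the prescription cannot meet, and the effect size passed to the next trial would belong to a regimen that the protocol does not describe. Sets and loads that are not recorded at the visit are hard to recover later.

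**Working it through.** **Inputs, all from the protocol:** 3 visits a week for 6 weeks; one-hour visits split 15 + 30 + 15 minutes; six resistance exercises (Table 2); 3 sets of 8-12 repetitions; 2-4 minutes of recovery between sets and between exercises; progression over 8 weeks.

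**The plan's own figures reproduce.**
- Visits: 3 × 6 = 18, as stated.
- Payment: 18 × $5 + 2 × $50 = $190, as stated in III.G.
- Visit: 15 + 30 + 15 = 60 minutes, which fills the hour exactly.

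The 6-week length is thus used consistently, and the 8-week progression is the figure that does not fit with it.

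**Check 1, progression.** 8 − 6 = 2 weeks. The stated end of the progression falls two weeks after the last training week. This needs no assumption.

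**Check 2, rest time.**
- Sets: 6 × 3 = 18.
- Recoveries: 18 − 1 = 17 (12 between sets of the same exercise, 5 between exercises).
- Rest: 17 × 2 = 34 minutes to 17 × 4 = 68 minutes, against 30.
- Even with no lifting time, fitting 17 rests into 30 minutes allows 30 / 17 = 1.76 minutes each, below the 2-minute minimum.
- Visit with rests only: 15 + 34 + 15 = 64 to 15 + 68 + 15 = 98 minutes, against 60, before lifting or stretching.

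**Check 3, lifting time (assumption).** The protocol gives no time per repetition. I assume 2-4 seconds.
- Lowest: 18 × 8 × 2 s = 288 s = 4.8 minutes.
- Highest: 18 × 12 × 4 s = 864 s = 14.4 minutes.
- Resistance block: 34 + 4.8 = 38.8 to 68 + 14.4 = 82.4 minutes, about 39-82.

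**Check 4, how far the result depends on the reading.** Rest time alone, at the 2-minute minimum:

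| Reading | Recoveries | Rest (min) |
|---|---|---|
| Six exercises, 3 sets (plain reading) | 17 | 34 |
| Five exercises, 3 sets | 14 | 28 |
| Six exercises, 2 sets | 11 | 22 |
| Six exercises, 3 sets, rests within an exercise only | 12 | 24 |

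The last three fit before lifting time is added. The protocol states neither the second nor the third, and the fourth goes against its wording, which puts rests between exercises as well. At 4 minutes, the fourth gives 12 × 4 = 48 minutes.

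**The case against.** The best case for the plan has three parts.

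*The programme is individualised.* Section II.E.2 fits both components to ability and adjusts progression every two weeks, and II.F.1 says that participants do only the exercises they are comfortable with. No sentence requires all six exercises at every visit. This stands in part: some participants may have a session that fits. But no rule says what is left out. Nor does individualisation explain the 8 weeks, since it sets the pace within a programme that still ends at week 6.

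*The feasibility criterion survives.* A reader might infer that, because the prescription overruns, hardly any session could count as completed and the 80% threshold would fail by construction. The documents do not support that. Section III.G speaks of completed and attended visits interchangeably, so the proportion can be read as visits attended out of 18, which rest length does not affect. A fuller definition might also sit in an analysis plan that is not at hand, so its absence is not an error in itself. An analysis plan could not, however, reconcile contradictory training instructions.

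*The pilot would reveal the problem.* Time in training is measured, so an overrun would be seen, and nothing says that delivered sets and loads go unrecorded. This is fair. Still, time in training alone does not show which sets or loads were given.

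A reader might also want to calculate the load reached at week 6. The protocol does not allow it: adjustment is every two weeks and individual, its shape is not given, and the 80% may be a ceiling.

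**Conclusion.** The point holds as an internal contradiction in the experimental prescription. The mismatch of two weeks between progression and programme rests on no assumption. The overrun of at least 4 minutes (34 against 30), and up to 38 (68 against 30), assumes only that a participant does all six listed exercises for three sets in one visit, which is the plain reading. Lifting time adds to it, but the total of about 39-82 minutes depends on the assumed 2-4 seconds per repetition. Stretching has no time in the hour on any reading that keeps the stated 15 + 30 + 15 minutes.

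The consequence is limited. Randomisation, eligibility, the frailty index, the Wilcoxon comparison and the retention criterion are untouched, and the completed-sessions criterion can be computed on attendance. What is weakened is interpretation: session completion, time in training and the effect size would not refer to a known, reproducible dose. That makes it a should-fix matter, not a fatal one.

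**What to change.** 1. The clinical team reconciles II.B, II.E.2 (including Table 2 and the text below it) and II.F.1 so that programme length, progression period, exercises, sets, rests, block length, stretching and visit length agree. Which values are right is a clinical decision, and none is proposed here. If individualisation is meant to shorten sessions, the text should say by what rule.
2. The protocol states whether a completed session means attendance or delivery of the reconciled prescription, and measures time in training against the same figures.
3. The training log records the sets and loads delivered at each visit, so that the dose behind the effect size can be reported.

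The cost is protocol wording and added entries on the training log. If the visit is lengthened, room scheduling and the time burden stated to participants change as well. The sample size and the planned analysis do not.

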#### F. Risk/benefit assessment:

1. **Physical risk:** The main risk of this study would be risks typically associated with exercise. Participants may experience shortness of breath, muscle soreness, dizziness, and increased heart rate. These effects typically resolve shortly after the exercise is stopped, however, muscle soreness may last a few days. Given the prevalence of fatigue in persons with MS, it is possible that participants will become fatigued during study visits. Additionally, the blood draw may present a risk to participants. Participants may experience momentary discomfort and bruising. Infection, excess bleeding, clotting and fainting are also possible although their occurrence is unlikely. Participants may also be at risk of falling during the exercise training. Injuries sustained from falling could range from mild, such as scratches and bruises, to severe, such as head injuries and/or bone fracture. There is also the risk of a data breach or unintentional disclosure, which is a risk to a participant in ANY research study. There is a risk of contracting COVID-19, which is also present in any research which involves face-to-face interaction between humans. Finally, the pressure pain threshold test may be uncomfortable for some individuals.

The first risk identified was the risk of incurring symptoms typically experienced during exercise. This risk will be mitigated in a variety of ways. Participants will be allowed breaks whenever they need it and be given access to water. Participants will only be

asked to complete exercises that they feel comfortable with. Additionally, the intervention program will be individualized based on the participant's abilities and will be readjusted every two weeks. Given the high rate of fatigue in persons with MS, it is possible that participants will become fatigued during study visits. To mitigate the risk of fatigue, participants will be given ample opportunity for rest during study visits. It is also likely that participants in the intervention group will experience temporary muscle soreness due to the resistance training aspect of the program. Each exercise session will begin and end with stretching to further minimize the risk of muscle pain. In addition, we will monitor perceived exertion through the Borg and Omni scales during each training session. We will also evaluate pain through the numeric pain rating scale during each training session (to differentiate this symptom from perceived exertion). If a participant reports a score higher than 3 on the numeric pain rating scale, we will stop the training session. To minimize the risk of musculoskeletal discomfort during maximal strength testing (1-RM assessment), we will use validated standard procedures for untrained individuals. To prevent participants from falling, participants will be encouraged to take a break if they feel tired, unwell, or dizzy. Participants will be spotted by a member of the research team and will wear an overhead harness that can be used to stabilize a participant if they were to become unsteady. In terms of the risks presented by the blood draw, the researchers will work to mitigate those risks by having the blood draw performed by trained clinicians in a sterile, cleaned environment, therefore minimizing risks.

Another risk identified was a data breach or unintentional disclosure. To prevent against this risk, several considerations have been made. Firstly, study personnel will receive HIPAA and information security training offered by the university. Any sensitive information will be stored in drives approved by the university for handling sensitive information. Participant information will also be stored in the Clinical Research Information System (CRIS), a system widely used by researchers, which offers secure protection for sensitive information. Any information that is not digital will be stored in secure locations by either the PI or study coordinator and will be secured by lock. Either the PI or study coordinator will hold the lock. Finally, the study team will only access protected information on a "as needed" basis. Protected information not relevant to the study will not be accessed by the study team. Participants will be informed of who will have their protected information and how it will be handled in the informed consent.

Another risk identified is the possibility of contracting or spreading COVID-19. This risk is present in any research where human beings meet face-to-face, even if the research does not involve human participants. The study team will follow all procedures, practices, and guidance set into place by the university. The study team will be fully vaccinated (including a booster shot). Masks will be worn according to university policy as well as researcher/participant comfort levels. Surfaces frequently touched will be cleaned and sanitized regularly. Hand sanitizer will be readily available in the lab and used by study team personnel and encouraged in participants any time there may be close contact between researchers and participants. 6-foot distancing will be followed when possible. Equipment used by participants (such as a safety harness) will be disinfected between uses.

The final risk that was identified is discomfort during the pressure pain threshold test. This will be mitigated by interrupting the test as soon as the participant reports any pain.

We also note that there were no serious adverse events in the 6-week virtual reality intervention in 108 persons with MS which serves as the foundation for the intervention

group. The safety of our approach is consistent with a systematic review highlighting the safety of exercise in persons with MS.

2. Psychological risk: None Known
3. Social risk: None Known
4. Economic risk: None Known
5. Potential benefit of participating in the study
  - a. As an interventional study, this proposal may provide benefits to participants. If the intervention is successful, participants assigned to the intervention could have an improvement in their frailty, which could improve health outcomes. Furthermore, participants assigned to the control group may also experience benefits associated with increased exercise if they decide to participate in the intervention after their final assessment. Benefits for both groups could include reduced fatigue, increased muscle strength, improved walking speed, and improved endurance. Additional benefits to participants can include a sense of pride for contributing knowledge to the greater scientific community, assisting researchers in better understanding their disease, and giving researchers information key to improve health outcomes in people with MS. Finally, participants will get to feel a greater sense of belonging to the MS community.
  - b. The proposed work will allow us to contribute more knowledge to the current literature regarding frailty and MS. The proposed work could allow us to contribute evidence regarding the dynamic nature of frailty in MS. It is not clear whether well-designed exercise-based interventions can reduce frailty in people with MS. Moreover, interventions in older adults designed to target frailty have had numerous methodological limitations – namely limited assessment of frailty prior to and post-intervention and lack of control group. The current study is designed to overcome these limitations and set the foundation for interventions to reduce frailty and maximize quality of life in pwMS.
  - c. While this research primarily benefits the MS community, additional benefits could be seen in science's general understanding of aging. Investigating why people with MS become frail earlier than people in other populations may inform how we view and understand frailty in general. Additionally, our investigation into exercise training to reduce frailty may not just benefit pwMS, but other individuals suffering from frailty as well. For humanity in general, this research could provide further evidence of the positive benefits that exercise can have on the human body.

**G. Location where study will be performed:** The screening visit will be performed at the KU Center for MS Care. The assessments (visits 2 and 3) will be performed in the Landon Center on Aging. The training visits will be performed at the laboratory for Advanced Rehabilitation Research in Simulation at KUMC.

**H. Collaboration (with another institution, if applicable):** N/A

**I. Single IRB Review for a Multi-site study (if applicable):** N/A

**J. Community-Based Participatory Research (if applicable):** N/A

